#### Follow-up survey

All indexes will complete a three-month follow-up survey online. The follow-up surveys will collect information of their experience of using the information packages, SST packages or referral link delivery; information on the relationship between the indexes and the alters; reasons of unwillingness to distribute; history of syphilis, HIV and other STIs testing in the past 3 months; and sexual behaviors in the past 3 months. Potential adverse events such as forced alters to test, received physical and/or verbal abuse, or being misunderstood from alters etc. during the delivery procures are asked.

### Cost data

A cost collection sheet will be used to identify, value and measure costs from the perspective of the program provider. This will include the start-up costs (e.g. packaging, peer notification card and result report card design, sites coordination, personnel training, pilot study), consumables (SST kits, standard of care testing supplies), capital costs (office equipment), and personnel costs. The time horizon will be the duration of the trial.

### Statistical methods

#### Sample size

We used an inequality test to calculate the sample size (PASS 15.0, NCSS, LLC). The details of the sample size calculation are shown in Table 2. Preliminary study results from the pilot RCT showed that the number of alters by an index was 0.05 through standard of care delivery, 0.60 through standard SST delivery, and 0.45 through SST link delivery. Based on the above data, we assumed that the variances of the three groups were equal with the same standard deviation of 0.8. Assuming the number of clusters will be allocated 1:1:1 to each arm, with cluster size of 10 per cluster, alpha of 0.05, power of 0.8, inter class correlation of 0.01, lost to follow-up rate of 0.20, we will need a minimum of 10 clusters per arm. To integrate the sample size calculations and to consider practicality, the final sample size would be ten clusters in standard SST delivery arm, ten clusters in SST referral link delivery arm, and ten clusters in standard of care arm, with a total cluster size of 30 (300 participants).

**Table 2 Tab2:** Sample size calculations

**SST and standard of care**	ICC	0.01
	Mean difference	0.55
	Standard deviation	0.8
	COV of cluster sizes	0.65
	Number of people per cluster	10
	Alpha	0.05
	Power	0.8
	Total sample size per arm	60
	Number of clusters per arm	6
**LINK and standard of care**	ICC	0.01
	Mean difference	0.4
	Standard deviation	0.8
	COV of cluster sizes	0.65
	Number of people per cluster	10
	Alpha	0.05
	Power	0.8
	Total sample size per arm	80
	Number of clusters per arm	8

*ICC* Intra-class correlation, *COV* Coefficient of variation

### Data analysis

#### Primary analysis

Sociodemographic characteristics will be summarized using descriptive statistics. The mean number of alters who returned photo verified syphilis testing result in each arm will be assessed using intention-to-treat analysis during the distribution period (3 months). The effects of the intervention will be measured by comparing the mean number of alters who returned photo-verified syphilis testing results in the three arms by using generalized estimated equations modelling to account for potential correlations in outcomes within groups. Egocentric network analysis will be used to describe the network characteristics, such as network size (i.e., the total number of alters in index’s disclosure network) [24].

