### Surveys

#### Baseline survey for index

All eligible indexes will complete a baseline survey online on the web-based survey platform Wenjuanxing (Changsha Haoxing Information Technology Co., Ltd., China) at enrollment. The baseline survey collects information on socio-demographic information, history of sexual behaviors, syphilis testing, HIV testing and other STIs testing, and their social network. Sociodemographic information includes age, biological sex, residence status, marital status, highest education, monthly income, sexual orientation, and whether they disclosed their sexual orientation with others. Sexual behaviors include sexual history with men and/or women, role during sex with men, condom use, type of sex partners, group sex, and drug use. Facility-based testing or self-testing history of syphilis, HIV and other STIs, and treatment experience will also be collected. A set of questions including a scale to measure social support, community leadership, and the size of their social network will be asked [24, 25].

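### The primary GEE names no baseline covariate, though network size and community leadership are measured in every index; adjusting for them and for site is a low-cost improvement

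*Protocol article*

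**What the plan says.** - **Primary analysis.** Arms are compared by intention to treat on the mean number of photo-verified alters over three months, "by using generalized estimated equations modelling to account for potential correlations in outcomes within groups". Handling correlation is the only purpose given for the model. No covariate is listed and none is ruled out.
- **Primary analysis, next sentence.** "Egocentric network analysis will be used to describe the network characteristics", with network size as the example. This is the only stated use of network data.
- **Baseline survey for index.** Among many other items, "a scale to measure social support, community leadership, and the size of their social network will be asked". No analysis section mentions leadership or social support again.
- **Secondary analysis.** A multivariable logistic model is planned for the proportions of first-time and of positive testers. This is the only place where a multivariable model is named for an effect comparison.
- **Randomization and allocation; Blinding.** Clusters are filled by ten successive attenders and randomised in blocks of three within each site. The schedule is given to the sites in advance, and the trial is open.
- **Sample size.** Expected means are "0.05 through standard of care delivery, 0.60 through standard SST delivery, and 0.45 through SST link delivery", with "variances of the three groups were equal with the same standard deviation of 0.8", "inter class correlation of 0.01" and "alpha of 0.05, power of 0.8". The result is 10 clusters per arm.

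**The concern.** The outcome is how many men an index gets to test. How many men he knows, and his standing among them, are natural candidates to predict that count. The Background section points the same way when it attributes the acceptability of network distribution to trusted community leaders.

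If these scores do predict the outcome, leaving them out has two consequences. Between-index variation that could be explained stays in the standard error. Any difference between arms in how well connected the indexes are also stays in the estimate. Such a difference can arise by chance with 10 clusters per arm, or through recruitment, because site staff who hold the schedule know which arm is being filled. The comparison most exposed is standard SST against referral link, where the expected difference is smallest.

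**Working it through.** **1. The plan's own figure.** Inputs from Sample size and Table 2: difference 0.40 (link versus control), SD 0.8, ICC 0.01, "COV of cluster sizes" 0.65, cluster size 10, alpha 0.05 (taken as two-sided), power 0.80, loss 20%.

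- Individuals per arm: 2 × (1.96 + 0.842)² × 0.8² / 0.40² = 62.8, so 63.
- Design effect: 1 + ((0.65² + 1) × 10 − 1) × 0.01 = 1.132.
- 63 × 1.132 = 71.3, so 8 clusters; 8 / (1 − 0.20) = 10. The stated 10 clusters per arm reproduce without any covariate.
- For the difference of 0.55, the same formula gives 34 × 1.132 = 38.5, so 4 clusters (5 with a t test), against 6 in Table 2. That row is conservative and does not drive the total.

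**2. Power without adjustment, difference 0.40.**

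- Ten per cluster: SE = 0.8 × √(2 × 1.132 / 100) = 0.120; power 91% (88% with t on 18 df).
- Eight per cluster after 20% loss: SE 0.133; power 85% (81% with t).

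The 80% target is met. If the ICC were 0.05 (an assumption), power with ten per cluster would be 78.3%, and covariates explaining 10% of the variance would bring it to 82.4%.

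**3. Possible precision gain.** The article gives no association between any score and the outcome, so strength is assumed over a range. Trials of 3 × 10 clusters of ten were simulated with the plan's means. The first simulation used Poisson counts capped at 6, a log-normal cluster effect with SD 0.2, one standardised score, and a Poisson GEE with independence working correlation (600 trials per setting). A second simulation added a useless second covariate. The table gives the ratio of unadjusted to adjusted variance for the log rate ratio of SST to link:

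| Rate ratio per SD | One score | With useless second covariate |
|---|---|---|
| 1.0 | 1.00 | 0.99 |
| 1.3 | 1.02 | 1.04 |
| 1.5 | 1.07 | 1.07 |
| 2.0 | 1.28 | 1.20 |

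For SST versus control the gain was 1–6% in the first and 0–7% in the second. The reason is visible in the expected counts. Control yields 100 × 0.05 = 5 events and SST 100 × 0.60 = 60, so on the log scale the Poisson part of the variance is about 1/5 + 1/60 = 0.217. Of this, 0.200 comes from control, and no covariate can remove it.

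On the mean-difference scale, covariates explaining 5% to 30% of the variance (assumed) multiply the SE by √0.95 = 0.975 to √0.70 = 0.837, a cut of 2.5% to 16%.

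**4. Size of chance imbalance.** The SD of the arm difference in a standardised score is √(2 × 1.132 / 100) = 0.150 if the score has ICC 0.01, so its 95% limits are ±0.30 SD. With a score ICC of 0.10 (design effect 2.32) they are ±0.42 SD. At an assumed correlation of 0.3 with the outcome, the shift is 0.295 × 0.3 × 0.8 = 0.07 to 0.422 × 0.3 × 0.8 = 0.10 alters per index. That compares with 0.40 for link versus control and 0.60 − 0.45 = 0.15 for SST versus link.

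**5. What adjustment cannot do.** For SST versus link, 0.15 / 0.120 = 1.25 SEs, giving power of about Φ(1.25 − 1.96) = 24%. Even with 30% of the variance explained (SE 0.101), it is Φ(1.49 − 1.96) = 32%.

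**The case against.** The strongest objection is that the article is silent rather than wrong. A reader might infer that the plan commits to an unadjusted model. Primary analysis does not say so, and a covariate list is commonly left to a full protocol or SAP, neither of which is shown. This stands, and it makes the point a recommendation. That the article names a multivariable model for the secondary proportions but no covariates for the primary GEE makes the gap worth closing, but does not prove a choice.

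A reader might also infer that the trial collects these scores as known drivers of distribution. The article lists them among many survey items and reports no association with the outcome, so their relevance is plausible, not documented.

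Third, a reader might take the shifts in step 4 for bias. Under valid randomisation, chance imbalance is variance that the standard error already carries. Only selective recruitment would bias the comparison. The article makes that possible but does not show it, and a few self-reported scores would correct it only in part.

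Finally, the larger gains concern SST versus link, which has no row in Table 2 and which the aim only sets out to explore. At the top of the range, a rate ratio of 2.0 per SD means a fourfold difference (2²) between men one SD above and one SD below the mean, which is a strong predictor. This also stands.

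**Conclusion.** As published, the primary GEE has no stated baseline covariates, although network size and leadership are available for every index and randomisation is blocked by site. That is a missed improvement. It is not an error or a contradiction, and it does not threaten the planned power against standard of care.

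The expected benefit is about 0–7% in effective sample size for standard SST versus control and about 0–28% for SST versus link, over assumed rate ratios of 1.0 to 2.0 per SD. The variance ratio of 0.99 with two uninformative covariates shows that the cost is negligible if the scores turn out not to matter. Site was not part of the simulations as described, so these figures belong to the scores alone. Adjustment would also take measured imbalance out of the estimate and, if fixed now, would prevent covariates being chosen after an imbalance is seen. It would not make SST versus link a well-powered comparison.

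**What to change.** In Primary analysis, prespecify the primary GEE as adjusted for:

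- baseline network size, entered as log(size + 1) because an index may report a disclosure network of zero;
- baseline community leadership score;
- site, the factor within which clusters are blocked.

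Report the standardised mean number of alters per index by arm, which keeps the result in the unit of the primary outcome. Keep the unadjusted GEE as a sensitivity analysis.

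Arms and interventions already places the hand-over of materials after the baseline survey. Add that the survey is completed before the index learns his arm, so that self-reported scores cannot be affected by allocation.

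The cost is a few sentences and no new data. A few missing baseline items will need simple imputation. The mean model would have seven parameters (intercept, two for arm, two scores, two for site) on 30 clusters and about 5 + 60 + 45 = 110 expected events. That is workable, though a small-sample correction to the robust variance would be sensible. Selection at recruitment would be corrected only partly.

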#### Secondary analysis

Within each arm of the study, we will calculate the proportion of first-time testers and testers with a positive syphilis testing result. Differences in proportions of first-time testers and testers with a positive syphilis testing result among alters during distribution period will be explored using Chi-square test and logistic regression in a multivariable model. We will also use descriptive analysis and chi-square test to compare the incidence of adverse events in three arms.

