### Randomization and allocation

At each site, eligible indexes will be assigned to one of the three arms through a cluster randomization procedure with ten participants per cluster. To ensure equal number of clusters in each of the three arms, the clusters will be randomized in a block of three at each study site. Computer-generated randomization codes will be produced and kept by a biostatistician who is not involved in participant enrollment. Ten blocks will be generated in total. Each block has three clusters consisting of standard of care arm, standard SST delivery arm, and referral link SST delivery arm, randomly created from all possible permutations. The schedule will be determined before the start of the study and then provided to each site. Each eligible index who presents to the site during a given 10-person cluster will be provided the allocated program. To reduce contamination between groups, eligible indexes will be allocated into the same group if they come in pair.

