#### Alter survey

Each alter in the three arms will receive an online survey link after uploading their syphilis test results. The survey will be created on the Wenjuanxing platform and includes questions on the relationship between the indexes and the alters, sociodemographic information, sexual behavior, the experience of receiving syphilis testing packages or links, testing history of syphilis, HIV and other STIs, and social network. The experience of accepting syphilis testing packages or links includes the behavior of the indexes when delivering syphilis testing packages or links, and the satisfaction to the delivery process of syphilis testing packages or links. Adverse events will be asked to identify whether the alters were being forced to test, have received physical and/or verbal abuse, or being misunderstood from indexes etc. during the delivery procedures.

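### Secondary alter-level comparisons use a plain chi-square test despite cluster randomisation, with only about 5 control alters expected and denominators formed after randomisation

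*Protocol article*

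**What the plan says.** All references are to the protocol article.

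- **Secondary analysis.** Proportions of first-time testers and of positive testers are calculated within each arm. Differences between arms "among alters during distribution period will be explored using Chi-square test and logistic regression in a multivariable model". For harms the text reads: "We will also use descriptive analysis and chi-square test to compare the incidence of adverse events in three arms". No population is named for the adverse-event comparison, and no logistic model is planned for it.
- **Randomization and allocation.** Indexes are assigned "through a cluster randomization procedure with ten participants per cluster".
- **Primary analysis.** The mean number of alters with a verified result is compared "by using generalized estimated equations modelling to account for potential correlations in outcomes within groups".
- **Sample size.** In the pilot, "the number of alters by an index was 0.05 through standard of care delivery, 0.60 through standard SST delivery, and 0.45 through SST link delivery". A common SD of 0.8 is assumed, with ten clusters of ten indexes per arm.
- **Alter survey.** "Each alter in the three arms will receive an online survey link after uploading their syphilis test results". This survey asks about testing history and adverse events.
- **Follow-up survey.** All indexes are also asked about adverse events at three months.
- **Secondary outcomes.** Positivity is defined with testers as the denominator.

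**The concern.** Three features of the secondary comparisons do not fit the design.

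First, each index starts with three packages or links and can obtain more. Alters of one index are his partners or friends, and indexes sit within randomised clusters. Testing history and infection status are likely to be correlated within these groups. The primary analysis allows for correlation; a plain chi-square test cannot, so its p-values would be too small.

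Second, the control arm is planned to yield very few tested alters, so a large-sample test or a multivariable model has little to work with there.

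Third, an alter enters the first-time and positivity denominators only by returning a result, and that is the primary outcome the interventions are meant to change. An arm that reaches many more men may reach a different mix of men. As an invented illustration, 3 of 5 control alters (60%) against 24 of 60 SST alters (40%) looks worse for SST, although SST found eight times as many first-time testers. Covariate adjustment does not restore the randomised comparison.

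**Working it through.** **Step 1: the planned arm size.** For link versus control (difference 0.40, SD 0.8, two-sided alpha 0.05, power 0.80):
- n per arm = 2 × (1.960 + 0.842)² × 0.8² / 0.40² = 62.8.
- Design effect = 1 + [(1 + 0.65²) × 10 − 1] × 0.01 = 1.132.
- 62.8 × 1.132 = 71.1, which needs 8 clusters (80 indexes); 80 / 0.80 = 100.

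This reproduces the plan's 10 clusters, or 100 indexes, per arm. The six clusters listed for SST versus control are more than the same formula needs, but that comparison is not binding and does not matter here.

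**Step 2: expected tested alters.** Table 2 uses 0.60 − 0.05 = 0.55 and 0.45 − 0.05 = 0.40 as the mean differences for the design, so the pilot rates are read as tested alters per index.

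| | Control | SST | Link |
|---|---|---|---|
| 100 indexes | 5 | 60 | 45 |
| 80 indexes (20% loss) | 4 | 48 | 36 |

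If the control total is Poisson with mean 5, its 95% range is about 1 to 10. Alters of secondary indexes are not in these figures and may add a few.

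**Step 3: expected cells in the three-arm table.** With 5 control alters and an assumed common proportion p, the control cells are 5p and 5(1 − p):
- p = 5%: 0.25 and 4.75; the positive cells in the other arms are 3 and 2.25, also below 5.
- p = 10%: 0.5 and 4.5.
- p = 30%: 1.5 and 3.5.
- p = 50%: 2.5 and 2.5.

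Both control cells are below 5 in every case. The chance of no positive control alter is about exp(−5p): 78% at p = 5%, 61% at 10% and 37% at 20% (assumed values). With no positives the control odds are zero, and ordinary logistic regression has no finite estimate of the effect against control. Even an observed 2 of 5 has an exact 95% interval of about 5% to 85%.

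**Step 4: the cost of ignoring within-index correlation.** The relevant group size is the size-weighted number of alters per index, E[X²]/E[X] = (SD² + mean²)/mean:
- SST: (0.64 + 0.36) / 0.60 = 1.67.
- Link: (0.64 + 0.2025) / 0.45 = 1.87.

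The documents give no within-index correlation; 0.2 to 0.4 is assumed. Design effect DE = 1 + (m − 1)ρ:
- Lowest: 1 + 0.67 × 0.2 = 1.13.
- Highest: 1 + 0.87 × 0.4 = 1.35.

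True size of a nominal 5% two-arm test = 2 × [1 − Φ(1.96/√DE)]: 6.6% at DE 1.13 and 9.2% at DE 1.35. For the three-arm test (2 degrees of freedom), size = exp(−5.99/(2·DE)), about 7% to 11%.

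This is a large-sample approximation using the two SST arms, so it suits SST versus link best. Against a control arm of 5 alters, the small cells of step 3 are the larger problem.

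**Step 5: wider cluster correlation.** With 6 (SST) or 4.5 (link) alters per cluster and the plan's COV of 0.65, DE = 1 + [(1 + 0.65²)m − 1] × ICC. At the planning ICC of 0.01 this is 1.05 to 1.08. That ICC was set for the index-level count, however. At assumed alter-level ICCs of 0.05 to 0.20, DE is about 1.3 to 2.5.

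**The case against.** These are secondary outcomes, described as explored, and the primary analysis and sample size are untouched. Yield among testers is a legitimate programme measure and a defined outcome, and the plan begins by reporting it within each arm. Reach is captured by the primary outcome, and the economic evaluation counts cases diagnosed, so a wide-reaching arm would not be judged on proportions alone. All of this stands. It lowers the severity and argues for keeping the proportions, but it does not make a plain chi-square test valid or a between-arm test of these proportions a randomised comparison.

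Some stronger readings are tempting but not supported:

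- A reader might infer that adverse events are compared by logistic regression among alters only, so that the harm comparison has an arm-dependent denominator. The plan names only descriptive analysis and chi-square for them, and indexes in all arms are also asked. The selection problem applies to alter-reported events.
- A reader might infer that the logistic model ignores clustering. The article is silent on its variance estimator, and a condensed article may leave that to the full plan. Only for the chi-square test does the fault follow from the named method.
- A reader might assume two to three alters per contributing index and reach a test size near 14%. The stated means and SD imply 1.7 to 1.9.

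The 5 control alters are an expectation from a pilot rate, not a fixed count.

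**Conclusion.** The point holds for the secondary analyses. The named chi-square test does not fit the cluster design. Its true size is about 6.5% to 9% for a nominal 5% two-arm test, given the plan's means and SD, an assumed within-index correlation of 0.2 to 0.4 and no further cluster correlation. With about 5 control alters expected, both control cells are below 5 at every proportion considered, and the logistic arm effect may not be estimable. These counts rest on the pilot rates and leave out alters of secondary indexes. Arm differences in first-time testing and positivity among testers should not be read as randomised effects; this conclusion needs none of the numerical assumptions.

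It would go too far to say that the proportions should not be reported or that the trial's main conclusion is at risk. This should be corrected before analysis, but it is not a critical defect.

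**What to change.** Amend the Secondary analysis section as follows.

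1. Keep the proportions of first-time and positive testers as descriptive outcomes by arm, with exact or cluster-robust intervals.
2. Base the between-arm comparison on the number of first-time-testing alters and of positive alters per randomised index. Include all 300 indexes, with zeros counted, and use the primary GEE framework. Say in advance what will be reported if the control arm has no positive alter, since a ratio to control would then have no finite estimate.
3. State that any alter-level test or logistic model accounts for clustering and is exploratory.
4. Compare adverse events per index from the follow-up survey, allowing for clustering. Report alter-reported events descriptively, noting that only alters who uploaded a result were asked.

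The cost is wording only, because the data are already to be collected. The downside is that the between-arm test moves from proportions to counts per index, which answers a different question, and the intervals become somewhat wider.
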